## Abstract

**Background:**

: Evacuation disorders are common in industrialized countries, affecting an average of 15% to 20% of the healthy adult population. Probiotic therapy can reduce functional constipation and increase both the number of weekly bowel movements and quality of stools. Based on the hypothesis that a combination of more strains may provide better results for constipation and facilitate adherence to treatment, this study will evaluate the efficacy and safety of a combination of different strains of *Lactobacillus* sp. and *Bifidobacterium* sp. in functional constipation.

**Methods:**

: A single-centre trial of adults aged 20 to 80 years with intestinal constipation will be conducted at a Gastroenterology Clinic in Sorocaba, State of São Paulo, Brazil. Participants will be allocated into 3 groups receiving:

The outcomes of interest will be change in frequency of weekly bowel movements, change in stool quality according to the 4–6 Bristol scale, number of volunteer withdrawal, number of adverse events and number of serious adverse effect.

**Discussion::**

The probiotic products are expected to induce beneficial changes in the intestinal microbiota, thereby increasing intestinal frequency to over 3 times a week and improving stool quality. The results can guide patients and healthcare practitioners and help in decision-making in the treatment of functional constipation.

**Trial registration and registry name::**

ClinicalTrials.gov Identifier: NCT04437147: The Effect of Probiotics on Functional Constipation in Adults: Study protocol for Double blind, Randomized, Placebo controlled Study

**Protocol Version::**

Version 01 August 30, 2020.

## Introduction

1

Of the gastrointestinal disorders, constipation is one of the most reported conditions in clinical practice.^[1,2]^ Constipation affects 15% to 20% of adults, of which 33% are over 60 years old, with predominance in females. The medical history of patients with constipation should be analyzed together with parameters such as fecal consistency, defecator frequency, effort when defecating, feeling of incomplete evacuation, abdominal pain and discomfort, use of laxatives, surgical history, comorbidities, lifestyle and work activity.^[3]^ Functional constipation is based on symptoms of nonorganic origin and diagnosed by the diagnostic criteria of Rome IV.^[4]^ The Bristol stool scale can help patients assess and describe aspects of their stool, facilitating the recognition of constipation severity.^[5]^ Please see Annex A in supplemental digital content.

Intestinal constipation impacts quality of life and can lead to significant costs in the search for treatments and purchase of laxatives.^[1,6]^ The treatment of constipation is a challenge in that are used osmotic, stimulating, irritating, and prokinetic laxatives.^[2]^ However, it appears that up to 47% of patients are not completely satisfied due to inconsistent response to laxatives and concerns about their safety, adverse effects, taste, inconvenience, and cost.^[7]^

Currently, it is known that there is an important interaction between microbes and intestinal physiology. Therefore, probiotics have been used to treat many intestinal problems,^[8]^ such as infectious diarrhea, diarrhea associated with antibiotics, diarrhea associated with *Clostridium difficile*, hepatic encephalopathy, ulcerative colitis, irritable bowel syndrome, functional gastrointestinal disorders, necrotizing enterocolitis, and functional constipation.^[9–11]^

Although the human microbiome comprises more than 400 bacterial species, evidence has shown that a decrease in the population of *Bifidobacterium* and *Lactobacillus* in adults can result in intestinal constipation.^[12–14]^ Consequently, the probiotics used in humans for the treatment of constipation are more often of the species *Lactobacillus* and *Bifidobacterium*. According to Ceresola et al.^[8]^ these *Lactobacillus* and *Bifidobacterium* can shorten the migratory myoelectric complex period and accelerate small intestine transit, partly due to increased release of serotonin (5-HT) which has promotility effects.

Clinical trials evaluating different strains of *Lactobacillus* and *Bifidobacterium* in the treatment of intestinal constipation have observed promising results,^[15–19]^ as well as systematic review on the topic.^[20]^ However, there is no consensus on probiotic strains and dosages for the treatment of constipation.^[12,21]^

Strain selection is an important step in the production of a probiotic. Probiotics should have a beneficial effect on the host and remain viable throughout the product lifetime.^[22]^

This clinical trial will evaluated the efficacy and the safety of 2 different probiotic formulations compared to placebo. One of them is composed by 4 strains of *Lactobacillus* (*acidophilus, rhamnosus, paracasei, and casei*) and 4 strains of *Bifidobacterium* (*bifidum, longum, lactis, and animalis*), given these are widely used in the treatment of adults with functional constipation. The other formulation will constitute 2 strains of *Lactobacillus* (*acidophilus, rhamnosus*) and 1 strain of *Bifidobacterium* (*bifidum*). Thus, this study will be to confirm whether these quantity of strains significantly influence constipation.

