#### Active comparator: 3 billion CFU strains of probiotics

2.3.1

*Lactobacillus acidophilus* LA 02 ID 1688 1 billion CFU, *Bifidobacterium bifidum* BB 01 ID 1722 1 billion CFU, *Lactobacillus rhamnosus* LR 04 ID 1132 1 billion CFU, vitamin C (ascorbic acid) 45 mg, vitamin B1 (thiamine) 1.1 mg, vitamin B2 (riboflavin) 1.1 mg, vitamin D-3 40,000,000 IU/g (cholecalciferol) 34 mcg, magnesium hydroxide 0.3 g, calcium carbonate 0.5 g, natural vanilla flavor powder 0.03 g, Fos (fructooligosaccharides) qsp 3 g, for 30 days, once daily in the form of sachet.

Assigned interventions: Dietary supplement of fibers plus vitamins and minerals will be administered for 30 days once daily in sachets containing 3 billion CFU strains of probiotics

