#### Active comparator: 8 billion CFU strains of probiotics

2.3.2

*Lactobacillus paracasei* LPC 00 ID 1076 1 billion CFU; *Bifidobacterium longum* BL 03 ID 1152 1 billion CFU; *Bifidobacterium lactis* BS 01 ID 1195 1 billion CFU; *Lactobacillus casei* LC 03 ID 1872 1 billion CFU; *Bifidobacterium animalis* LMG 10508 1 billion CFU*; Lactobacillus acidophilus* LA 02 ID 1688 1 billion CFU, *Bifidobacterium bifidum* BB 01 ID 1722 1 billion CFU, *Lactobacillus rhamnosus* LR 04 ID 1132 1 billion CFU, vitamin C (ascorbic acid) 45 mg, vitamin B1 (thiamine) 1.1 mg, vitamin B2 (riboflavin) 1.1 mg, vitamin D-3 40,000,000 IU/g (cholecalciferol) 34 mcg, magnesium hydroxide 0.3 g, calcium carbonate 0.5 g, natural vanilla flavour powder 0.03 g, Fos (fructooligosaccharides) qsp 3 g, for 30 days, once daily in the form of sachet

Assigned interventions: Dietary supplement of fibers plus vitamins and minerals will be administered for 30 days once daily in sachets containing 8 billion CFU strains of probiotics.

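### The 8-strain and 3-strain sachets differ in strain number, total CFU and strain identity at once, so the stated aim of confirming an effect of strain number cannot be met and should be reworded as a comparison of two formulations

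*Protocol article*

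**What the plan says.** The Abstract (Background) motivates the trial with the "hypothesis that a combination of more strains may provide better results for constipation". The Introduction describes the two products: for the larger, "One of them is composed by 4 strains of" *Lactobacillus* and four of *Bifidobacterium*; for the smaller, "The other formulation will constitute 2 strains of" *Lactobacillus* and one of *Bifidobacterium*. It then concludes: "Thus, this study will be to confirm whether these quantity of strains significantly influence constipation".

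Section 2.3.1 lists three strains, each with its own count (for example "LA 02 ID 1688 1 billion CFU" for *L. acidophilus*), and sums them up as "sachets containing 3 billion CFU strains of probiotics". Section 2.3.2 lists eight strains at the same count each and sums them up as "sachets containing 8 billion CFU strains of probiotics". Sections 2.1 and 2.6 also identify the active arms by CFU.

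The Discussion returns to the comparison of the 8-strain with the 3-strain product and asks which performs better. The only limitation it names is reliance on self-report.

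**The concern.** The Introduction uses confirmatory language for one specific feature, the number of strains. The design does not vary that feature by itself: the product with more strains also has a larger total live count and contains strains that the other product lacks.

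If the 8-strain arm did better, the natural reading under the stated aim would be that more strains help, although the cause could be the larger total count or a single effective strain among those added. If the arms did not differ, the natural reading would be that strain number does not matter, which would be equally unsupported. The Introduction itself says that dosage, as well as choice of strain, is unsettled in this field, so total CFU is not a factor that the authors can treat as known to be inert. The Abstract expects the results to guide patients and practitioners, so a wrong attribution could carry over into how products are chosen.

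**Working it through.** **Inputs**

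- Strain counts (Introduction): 2 + 1 = 3 and 4 + 4 = 8.
- CFU per strain (sections 2.3.1 and 2.3.2): 1 billion for every listed strain in both products.
- Control (section 2.3.3 and Discussion): no probiotic strains, so 0 strains and 0 CFU.

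**Step 1. Reproduce the stated totals**

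- 3 strains × 1 billion = 3 billion CFU, as stated.
- 8 strains × 1 billion = 8 billion CFU, as stated.
- Ratio of strain numbers: 8/3 = 2.67. Ratio of total CFU: 8/3 = 2.67.

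**Step 2. Compare the lists**

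- Shared, at equal amounts: *L. acidophilus* LA 02, *B. bifidum* BB 01, *L. rhamnosus* LR 04.
- Only in the 8-strain sachet (8 − 3 = 5): *L. paracasei*, *B. longum*, *B. lactis*, *L. casei*, *B. animalis*.
- The vitamins, minerals, flavour and fructooligosaccharides listed are the same in both active sachets.

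Three features therefore change between the active arms: strain number, total CFU and strain identity. CFU per strain is constant.

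**Step 3. Can the features be separated?**

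Write the expected outcome in an arm as *a* + *b* × (strain number) + *c* × (total CFU in billions).

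| Arm | Intercept | Strain number | Total CFU (billions) |
|---|---|---|---|
| Placebo | 1 | 0 | 0 |
| 3-strain | 1 | 3 | 3 |
| 8-strain | 1 | 8 | 8 |

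The last two columns are identical. Their correlation is 1.0, and the matrix has rank 2 for 3 columns. Only the sum *b* + *c* can be estimated.

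The contrast between the active arms is (8 − 3)*b* + (8 − 3)*c* = 5(*b* + *c*). Adding a term *d* for the particular effect of the five extra strains gives 5*b* + 5*c* + *d*: one observable difference for three unknowns. A difference D fits equally well with *b* = D/5 and the others zero, with *c* = D/5 and the others zero, or with *d* = D and the others zero. A difference of zero shows only that the sum is zero, not that *b* is.

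The linear form is for illustration. Without it there is still a single contrast between two products that differ in three respects. The sample size does not enter, so neither more patients nor an analysis plan that is not shown could change the result.

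**The case against.** The strongest reply is that the trial is mainly about something else and that much of the text is already at the level of whole products. Section 2.1 sets the superiority hypothesis as probiotics against placebo, and section 2.10 anticipates a rise under treatment with no change on placebo. The Introduction paragraph that contains the disputed sentence opens by describing two formulations compared with placebo. The Discussion asks which combination acts better, which is a question about formulations. The arms are labelled by CFU, so the difference in total count is in plain view. In the Abstract, the idea that more strains help is a rationale and not the stated objective.

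All of this stands. It limits the reach of the point but does not remove the Introduction sentence, which names strain number as what will be confirmed. Nor does it supply the missing limitation.

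A second reply is that CFU per strain is held constant, so the 8-vs-3 contrast validly estimates the effect of adding five strains at 1 billion CFU each. That is also right. The collinearity in the working concerns strain number at fixed *total* CFU, and a design with equal totals would instead tie strain number to the amount per strain. But the add-on contrast is the effect of those five strains and their CFU together. It still cannot be credited to number alone.

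Three stronger conclusions are tempting and should be resisted:

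- **A reader might infer that the trial's main hypothesis will be settled by a confounded comparison.** The documents do not support this. The hypothesis in section 2.1 is against placebo, and no decision rule for strain number is given anywhere.
- **A reader might infer that 8 vs 3 has no stated power.** Section 2.5 claims 80% power between the three treatments. Whether that calculation serves each pairwise contrast is a separate sample-size question.
- **A reader might infer that 8 vs 3 must be labelled exploratory.** Confounding of the products' features limits attribution. It does not make a randomised comparison of two whole products any less valid.

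**Conclusion.** The point holds as a limit on attribution. The stated aim claims a property that the design does not have: with strain number and total CFU perfectly collinear (3/3 and 8/8), and with five strains present in one product only, no 8-vs-3 result can be ascribed to strain number. This follows exactly from the article's own composition lists and needs no outside assumption beyond taking the listed counts at face value.

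The comparison of each probiotic product with placebo is untouched by this, and so is the comparison of the two products as complete formulations. It is a correction of wording, but one worth making, because it changes what the trial may conclude. No judgement is made here on which dose or composition is preferable.

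**What to change.** - **Introduction:** replace the closing sentence on the quantity of strains with an aim to compare two complete formulations (3 strains with 3 billion CFU in total, and 8 strains with 8 billion CFU in total) with each other and with the control.
- **Abstract (Background):** align the rationale with that aim, so that it does not promise a test of strain number. The motivating idea may stay if it is clearly marked as background.
- **Discussion:** phrase the 8-vs-3 question as one about formulations. Add to the limitations that strain number, strain identity and total CFU vary together, and that no 8-vs-3 result, positive or null, will be interpreted as an effect of strain number alone.

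The cost is a few sentences. Products, arms, randomisation, outcomes and sample size stay as they are.

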## Methods

2

It is a singlecenter, controlled, randomized, and blinded clinical trial outlined in accordance with the criteria set out by the SPIRIT statement.^[23]^

### Study design and setting

2.1

This study is parallel and has the structure of superiority working with the hypothesis that the groups that will receive probiotics are more effective than the group that will receive the placebo (constituted of only fibers, vitamins, and minerals which is a conventional treatment for constipation).

Over a 4-week period, a singlecentre, double-blind, randomized, placebo-controlled study of 150 patients (50 patients per group) with functional constipation will be treated using probiotics containing 3 billion CFU of mixed strains probiotics containing 8 billion CFU of mixed strains or placebo.

The study will be conducted in Clinic of Gastroenterology [name] [name], localized in Sorocaba, State of São Paulo, Brazil. Patient recruitment for this study will be carried out through a collaborative effort between the University of Sorocaba and physician [name] that attending in Clinic of Gastroenterology. From the university, a flyer will be sent out via e-mail and letters distributed around Campus or messages texted via cell phone, and social media will also be exploited to promote the study.

The recruitment will be until the date of November 30, 2020. After verbal and written explanation, individuals who agreed to participate in the study will sign the Free and Informed Term of Consent already approved by the Ethics Committee of the University of Sorocaba (Annex B, supplemental digital content).

### Eligibility criteria

2.2

#### Inclusion criteria

2.2.1

Patients eligible for the trial are adults aged 20 to 80 years;Clinical diagnosis of functional constipation according to Rome IV. The Rome IV Consensus defines functional constipation as a dysfunction that manifests with difficult, infrequent and incomplete bowel movements. The constipation must have started 6 months previous and become more frequent in the last 3 months, including 2 or more of the following characteristic: involving <25% of bowel movements: effort, hardened resistance (Bristol scale 1–2), feeling of incomplete removal, sensation of anorectal obstruction, digital manoeuvres to facilitate the exit of fecal content, less than 3 spontaneous bowel movements/week and need for laxatives^[4]^;Granting of written informed consent.

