### Data analysis planning

2.10

Preliminary data indicate that the number of evacuations weekly is 2 or 3 times higher in patients than in control volunteers. The hypothesis is that treatment will likely increase the number of weekly bowel movements from 1 to 3 times to over 4 times a week, while no changes will be seen in the placebo group.

Anova will be used in order to compare continuous variables between the intervention and control groups. Score changes between the intervention and the control groups will be compared by Kruskall–Wallis.

Analysis of adverse events (if any) and the other outcomes will be performed using the Student *t* test and Mann–Whitney *U* test. In all measured will used the intention to treat analysis. The level of significance will be at *P* < .05. The raw data will be input into the statistical software. Statistical analysis will be performed at STATA v.14.2.

All data collected on paper will be marked with a research identification number to avoid identifying the participants and stored in a locked cabinet. Only the author of the research report can access these identified data sets.

The data monitoring committee is not necessary because the statistical analysts will be blind to evaluate the outcomes data.

Volunteers will be instructed to write down any adverse events on the attached form A and if they feel the need to interrupt treatment due to inconvenience that they are unable to continue and write down what the reactions were.

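### The inclusion criterion sets 25% as an upper limit on how often constipation features occur, against its own description of the condition and the diagnosis it spells out

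*Protocol article*

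**What the plan says.** Section 2.2.1 (Inclusion criteria) of the protocol article builds the diagnostic criterion in layers:

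- The governing requirement: "Clinical diagnosis of functional constipation according to Rome IV".
- A description of the condition, attributed to Rome IV: a "dysfunction that manifests with difficult, infrequent and incomplete bowel movements".
- A symptom course: "The constipation must have started 6 months previous and become more frequent in the last 3 months".
- A feature count: "including 2 or more of the following characteristic", followed directly by the qualifier "involving <25% of bowel movements: effort, hardened resistance (Bristol scale 1–2), feeling of incomplete removal". Anorectal obstruction and digital manoeuvres come next, and the list ends with "less than 3 spontaneous bowel movements/week and need for laxatives".

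Section 2.10 (Data analysis planning) expects that "treatment will likely increase the number of weekly bowel movements from 1 to 3 times to over 4 times a week", so the analysis has a clearly constipated population in mind. No other section gives a different threshold.

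**The concern.** A feature-count rule for a symptomatic condition should count a feature when it is common enough to matter. This one counts a feature when it is uncommon. The section therefore gives a screener two tests that can disagree about the same person: the diagnosis and the description point one way, and the spelled-out threshold points the other.

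The threshold is also badly placed. It stands ahead of the whole list, but the last two items (a weekly count and a need for laxatives) cannot occur in a share of bowel movements.

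What is at stake is a clear definition of the trial population. Screening has to apply one rule, and readers will use the published criterion to judge to whom the results apply.

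**Working it through.** No sample-size, power or error-rate figure underlies this point. The check is to apply the written feature count to hypothetical patients.

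**Inputs, all from section 2.2.1.** Five features have a share of movements: effort, hard stools, incomplete evacuation, obstruction and digital manoeuvres. Two do not: fewer than 3 spontaneous movements a week, and need for laxatives. At least two features are needed.

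**Rule.** Count = (number of the five with share below 25%) + (1 if fewer than 3 movements a week) + (1 if laxatives are needed). The count is met at 2 or more.

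**Three readings.** (i) Literal. (ii) Below 25%, but the feature must be present at all (share above 0). (iii) Inequality reversed (25% or more), used only to test direction.

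| Hypothetical patient | (i) Literal | (ii) Below 25% and present | (iii) Reversed |
|---|---|---|---|
| a. 5% on all five, 7 movements/week, no laxatives | 5, met | 5, met | 0, not met |
| b. 0% on all five, 7/week, no laxatives | 5, met | 0, not met | 0, not met |
| c. 80% on all five, 5/week, no laxatives | 0, not met | 0, not met | 5, met |
| d. 80% on all five, 2/week, no laxatives | 0 + 1 = 1, not met | 1, not met | 5 + 1 = 6, met |
| e. 80% on all five, 2/week, laxatives needed | 0 + 1 + 1 = 2, met | 2, met | 5 + 1 + 1 = 7, met |
| f. 80% effort and hard stools, 0% on the other three, 5/week, no laxatives | 3, met | 0, not met | 2, met |

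**Reading the table.** Patients a, c and d change sides when the inequality is reversed, under either reading of the text as it stands. Patient a, with each feature in one movement in twenty, meets the count. Patient d, with every feature in four movements out of five and only 2 movements a week, does not. Patients b and f depend on whether an absent feature can count as a characteristic. Patient e shows that frequent symptoms do not always fail the count.

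**Set against the section's own words.** Patients c and d fit the description of difficult and incomplete movements, and d is also infrequent; patient a fits none of it. The symptom-course sentence asks for constipation that is becoming more frequent, which sits badly with a cap on frequency. The contradiction can be shown without the Rome IV text.

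**Assumption.** The weekly count and the laxative item are taken as two separate features. If the closing phrase were read as one combined item, patient e would score 1 and fail as well.

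**The case against.** The strongest reply is that the governing criterion is a Rome IV diagnosis, supported by a citation, and that the list only paraphrases it. The clinic physician selects volunteers (section 2.6), and someone almost free of symptoms should fail both the diagnosis and the required symptom course. The table tests the feature count alone and leaves those joint conditions out. The sign may well be a typographical slip.

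Much of this stands. A reader might infer that the trial will enrol people without constipation, or shut out everyone with frequent straining or hard stools. The documents support neither. The joint conditions guard against the first, and patient e refutes the second, as does patient f on the literal reading.

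A reader might also infer that low weekly frequency goes unrequired because of the sign, in tension with the 1 to 3 movements a week assumed in section 2.10. That follows from needing any two features and would remain after the sign was reversed.

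The reply does not rescue the sentence. The diagnosis and its spelled-out test still disagree, and the sentence is part of the eligibility rule, not background.

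**Conclusion.** The point holds as an internal contradiction in the eligibility rule. The 25% threshold is written as an upper limit, the section's own description points to a lower one, and the qualifier is attached to two items that it cannot describe. A feature in 5% of movements counts and one in 80% does not. The Rome IV diagnosis, the symptom-course requirement and the route through low frequency plus laxatives limit the practical effect. How far they do so depends on which text the physician applies, and the documents do not settle that.

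Two further inferences are not supported. One is a loss of power from participants with no room to improve: the article gives no means, standard deviations or effect size, and nothing ties any share of such participants to the sign. The other is that participants could count as successes at entry: section 2.4.1 compares day 0 with day 30, and section 2.10 plans no test of responder proportions. No power figure and no change to the outcome rule follow from this point.

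**What to change.** In section 2.2.1, the sponsor should reconcile the direction of the 25% threshold with the cited Rome IV definition and with the section's own description. The description points to a lower limit, but the exact wording must come from the cited source, which is not reproduced in the article. The weekly-frequency item and the laxative item should be listed separately, outside the percentage qualifier, so that it governs only the features that have a share of movements.

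The cost is one corrected sentence. It adds no procedures, data or analyses and leaves the sample size unchanged.
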